## Abstract

**Background:**

Due to faster recovery and lower morbidity rates, laparoscopy has become the gold standard in elective colorectal surgery for both the benign and malignant forms of the disease. A substantial proportion of colorectal operations are, however, carried out in emergency settings, and most of the emergency resections are still performed open. The aim of this study is to compare the laparoscopic versus open approach for emergency colorectal surgery.

**Method/design:**

This is a multicenter prospective randomized controlled trial including adult patients presenting with a condition requiring emergency colorectal resection.

**Discussion:**

Previous studies cautiously recommend wider use of laparoscopy in emergency colorectal resections, but all earlier reports are retrospective, are mostly single-center studies, and have limited numbers of patients. Laparoscopy may involve some unpredictable risks that have not yet been reported because of the infrequent use of the techniqueded to assess the safety of laparoscopy as well as the advantages and disadvantages of open compared with laparoscopic emergency surgery.

**Trial registration:**

Trial registration number: ClinicalTrials.gov NCT05005117. Registered on August 12, 2021.

**Supplementary Information:**

The online version contains supplementary material available at 10.1186/s13063-024-08058-0.

## Background and rationale

The first laparoscopic colon resection for colorectal cancer was performed in 1990. In the beginning, there were concerns about achieving adequate oncological results with the laparoscopic technique. Additionally, there were considerable numbers of port site metastases in the 1990s which over time diminished along with the development of laparoscopic instrumentation [1]. Initial doubts were quite soon dispelled, and laparoscopy was proven to be both safe and equal to open surgery in terms of the oncological results [2–4]. Patient recovery was also faster, postoperative ileus occurred less often, and overall morbidity was lower [4–6]. As a result, laparoscopy proved to be cost-effective [7].

Today, laparoscopic colorectal resections are well established in elective surgery, although the role of laparoscopy in emergency operations remains uncertain [8, 9]. It may be expected that the same benefits achieved with minimally invasive techniques in elective surgery also advocate the use of laparoscopy in emergency operations [10–12]. There are, however, several concerns regarding laparoscopy in emergency settings. The operations are technically more challenging due to distortion of the normal anatomy and the presence of a dilated vulnerable bowel [13]. Intra-abdominal lavage in inflammatory processes might be less effective [14] and the operation takes longer, which could be a disadvantage for the critically ill patient [15].

Approximately 10–20% of colorectal resections are carried out as emergency operations, which are associated with a higher risk of in-hospital mortality, double the risk of reoperation, and a three times higher risk of failure to rescue, compared to elective surgery [16–18]. The type of complication varies greatly depending on whether the operation has been elective or emergency, which most likely also reflects the type of technical approach. For example, fascial rupture is almost three times more common after emergency surgery [18]. In many other entities demanding emergency surgery, the laparoscopic approach has proven to diminish both morbidity and mortality [19] and can therefore be assumed to do the same in colorectal surgery.

As many as 15–20% of patients with colorectal cancer present with an obstruction [16], and it is important that the oncologic results do not get worse when a new surgical technique is employed. There are no previous reports assessing oncologic outcome between the laparoscopic and open approaches in emergency operations. When assessing the oncologic adequacy of the surgical approach, the pathology report and the quality of the surgical specimen are of the utmost importance. Classifying the surgical specimen is only possible in a prospective study design. Benz et al. proposed a new classification system for surgical specimens that facilitates this evaluation [20].

Previous reports on laparoscopy for emergency colorectal resections cautiously propose using laparoscopy more often in emergency settings, although most of the reports are retrospective, register-based or single-center studies with limited numbers of patients [21–23]. The aim of this study is to evaluate whether patients benefit from the laparoscopic approach in emergency colorectal surgery in both the benign and malignant forms of the disease.

### Objectives

The objective of this study is to evaluate whether patients benefit from the laparoscopic approach in emergency colorectal surgery, whether benign or malignant disease.

Our hypothesis is that the same beneficial effects of laparoscopy seen in elective surgery and in other entities needing emergency surgery will also apply to emergency colorectal surgery. These benefits are lower overall postoperative morbidity, shorter in-hospital stay, less postoperative ileus, less postoperative pain, fewer wound complications, and lower risk of mortality.

For oncologic patients, our hypothesis is that the laparoscopic approach is superior to the open approach, partly because of the faster recovery associated with greater access to oncologic treatment and partly because in laparoscopy the intra-operative circumstances need to be optimized to mimic the elective situation, leading to good visualization and a standardized approach.

### Trial design

This study is a prospective, randomized, controlled, multicenter, superiority study comparing the laparoscopic and open approaches for emergency colorectal resections. The primary endpoint is postoperative morbidity. The trial is independent of any kind of commercial sponsorship. The flow chart of the study is presented in the (Fig. 1).

**Fig. 1 Fig1:**
[figure not shown]
Flowchart

## Methods

### Study setting

This study will be carried out in six university or central hospitals in Finland: Päijät-Häme Central Hospital, Pohjois-Karjala Central Hospital, Jorvi Helsinki University Hospital, Kanta-Häme Central Hospital, Keski-Suomi Central Hospital, and Oulu University Hospital.

### Eligibility criteria

#### Inclusion criteria

The patient has a condition necessitating emergency colorectal resection. We define the timeframe for emergency colorectal resection to be within 0–48 h from the decision to proceed with surgery.Age 18 years or olderThe patient is competent to give their consentSigned informed consent

#### Exclusion criteria

The patient’s condition is due to traumaSimultaneous acute pancreatitisThe need for resection is due to a complication from a previous procedure, i.e., reoperationSimultaneous ruptured aortic aneurysm or ruptured aortic aneurysm as the underlying cause of the need for surgery

All patients arriving in the emergency room and diagnosed with a condition requiring emergency colorectal resection will be considered for inclusion. After receiving proper information on the possible advantages and disadvantages of the intervention, and after voluntarily signing the informed consent form, the subjects will be enrolled in the trial. The written consent will be obtained by a member of the research group and a copy given to the patient. After enrolment, the patient will be randomized for either open or laparoscopic surgery. The procedure will be carried out or closely supervised by a specialist in gastrointestinal surgery experienced in colorectal resections. Patients considered but not meeting the inclusion criteria and patients with at least one exclusion criterion will not be enrolled. These patients and the reasons for their exclusion will be documented. Postoperative care and follow-up will follow normal praxis and the case report form will be completed. Ninety days after surgery, patients will be requested to fill in the Gastrointestinal Quality of Life Index (GIQLI) questionnaire, which is the only deviation from normal follow-up. The GIQLI questionnaire will be sent by post at no cost to the patient. Once enrolled, patients will not be required to make any further visits to the hospital or to undergo any radiation or medical procedures. The follow-up for oncology patients will also be arranged according to the normal follow-up schedule.

If at any point the allocated type of intervention needs to be modified or even discontinued because of patient safety or for any other reason, the circumstances and reasons will be carefully documented and the patient will be informed. For example, if the patient’s condition changes, making the patient unfit for surgery, the patient will normally be excluded. In the event of conversion during the operation, the circumstances will be carefully documented but the patient will still be able to participate.

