### Outcomes

The main endpoint of the study will be 30-day postoperative morbidity, which will be evaluated from the Comprehensive Complication Index (CCI) of all patients. CCI is the sum of all complications weighted on with their severity based on the Clavien-Dindo classification (CCI = √(*wC* + *wC*2 + … + *wCx*)/2) and has values ranging from 0 to 100 [24].

The secondary endpoints of the study are as follows.

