### Recruitment

All subjects fulfilling the inclusion criteria will be considered for participation in the trial. An anonymous record will be kept prospectively for all subjects fulfilling the inclusion criteria but not attending, either for not consenting or for any other reason, for later assessment of selection bias. The schedule of events in the study is shown in the Table 2.

**Table 2 Tab2:** SPIRIT figure

Schedule of events	Baseline	Procedure	Postoperative monitoring during hospital stay	Discharge	30 days	90 (+ 60) days	1 years	2 years	3 years	5 years	Unscheduled visit
Informed consent	X										
Need for preoperative intensive care/intensive care unit treatment	X										
Demographics and medical history	X										
Procedure details		X									
Need for postoperative intensive care/intensive care unit treatment			X								
Bowel function			X								
Analgesics			X	X							
Complications		X	X	X	X						
Gastrointestinal Quality of Life Index (GIQLI)						X					
Mortality						X					
Oncological patients: TNM classification, adjuvant chemotherapy, chemotherapy OS, CSS, DFS							X		X	X	X
Ostomy closure								X			
Protocol deviation	X	X	X	X	X		X		X	X	X

*OS* overall survival, *CSS* cancer-specific survival, *DFS* disease-free survival

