### Data management

All data will be handled with the utmost confidentiality. Patients’ CRFs will be filled in by the study personnel during postoperative monitoring. The data will then be entered manually in the electronic database (SPSS). All patients will be supplied with a research number and the keyfile connecting research number with patient identification number stored separately from the main dataset. Both files will be placed into locked storage, accessed only by research personnel on faculty computers accessed only with a personal password. At the end of the study period, all data will be destroyed. Permission for the study register has been given by the ethics committee of Helsinki University Hospital and by the Päijät-Häme Central Hospital administration.

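### Thirty-day complications are scheduled in both arms, but after discharge the plan relies on routine care to detect them, so minor events may be recorded less completely after laparoscopy

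*Protocol article*

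**What the plan says.** **Outcome.** Protocol article, Outcomes: "The main endpoint of the study will be 30-day postoperative morbidity, which will be evaluated from the Comprehensive Complication Index (CCI) of all patients". The index is defined there as a severity-weighted sum over all complications, so minor events count.

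**Follow-up.** The text under Exclusion criteria places postoperative follow-up within usual practice. It describes the posted 90-day GIQLI as a "questionnaire, which is the only deviation from normal follow-up" and adds: "Once enrolled, patients will not be required to make any further visits to the hospital or to undergo any radiation or medical procedures".

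**Recording.** Data management: "Patients’ CRFs will be filled in by the study personnel during postoperative monitoring". Table 2 (under Recruitment) has a column headed "Postoperative monitoring during hospital stay", separate from its Discharge and 30-day columns. The Complications row is marked at procedure, hospital stay, discharge and 30 days.

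**Expected stay and blinding.** Objectives lists among the hypothesised benefits of laparoscopy "lower overall postoperative morbidity, shorter in-hospital stay". Under Blinding, only the assessor of specimen photographs is said to be masked.

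**The concern.** Table 2 requires a day-30 complication entry, but the follow-up text provides no trial-specific means of obtaining it from a patient who has gone home. In hospital, complications are seen directly by study personnel. After discharge they are seen if the patient returns, or if routine records happen to hold them.

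If laparoscopic patients leave earlier, as the trial expects, a larger part of their 30-day window falls in the less closely observed period. The events at risk are mainly Clavien-Dindo I–II complications managed outside hospital.

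Two features make such a loss hard to correct later. First, Statistical methods removes cases with missing data, but an unrecorded complication is not a missing value: it scores as no event. Second, masked grading would not help, because an event that was never recorded cannot be graded. The error would favour the trial's own hypothesis.

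**Working it through.** **1. The passages side by side**

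| Question | Where | Answer |
|---|---|---|
| Window for the primary outcome? | Outcomes | 30 days |
| Is a day-30 complication entry scheduled? | Table 2 | Yes, both arms |
| Is a trial-specific contact provided to obtain it? | Exclusion criteria, follow-up text | No; the 90-day questionnaire is the only addition to usual follow-up |
| Which later events are collected as separate outcomes? | SSI; Reoperation risk; Readmission | Each to 30 days |
| Is the content of usual follow-up to day 30 stated? | Nowhere | – |
| Is discharge expected to be earlier in one arm? | Objectives | Yes, laparoscopic; no number of days given |

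The schedule and the follow-up text are compatible only if routine care already yields complete day-30 information in both arms. The article does not say that it does.

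**2. The plan's own figure**

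Inputs from Sample size and Statistical methods: p₁ = 0.483 (open), p₂ = 0.278 (laparoscopic), two-sided α = 0.05, power 80%. Mean rate p̄ = 0.3805.

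n = [1.960·√(2·0.3805·0.6195) + 0.8416·√(0.483·0.517 + 0.278·0.722)]² / 0.205² = (1.346 + 0.565)² / 0.0420 ≈ 87 per group.

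This agrees with the stated 87. The planned difference is 48.3 − 27.8 = 20.5 points. The calculation does not depend on the present point.

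**3. Illustration of the possible bias**

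The documents give no length of stay by arm, no share of complications arising after discharge and no share missed. All three are assumed here. The illustration uses the proportion of patients with any complication, because the sample size is set on that scale.

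- True rate 48.3% in both arms (no treatment effect), 87 per arm.
- f_open and f_lap: share of affected patients whose only complications arise after discharge.
- m: fraction of those patients missed, the same in both arms.
- Recorded rates: a = 0.483(1 − f_open·m) and b = 0.483(1 − f_lap·m).
- False difference: a − b = 0.483·(f_lap − f_open)·m.
- Type I error: Φ((d − c)/s) + Φ((−d − c)/s), with d = a − b, r the mean of a and b, c = 1.96·√(2r(1 − r)/87) and s = √((a(1 − a) + b(1 − b))/87).

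| f_open / f_lap | m | False difference (points) | Share of 20.5 | Type I error |
|---|---|---|---|---|
| any | 0 | 0 | 0% | 5% |
| 15% / 20% | 0.5 | 0.483·0.05·0.5 = 1.2 | 6% | 5.3% |
| 15% / 25% | 0.5 | 0.483·0.10·0.5 = 2.4 | 12% | 6.2% |
| 15% / 25% | 1 | 0.483·0.10·1 = 4.8 | 24% | 10% |
| 20% / 40% | 0.5 | 0.483·0.20·0.5 = 4.8 | 24% | 9.9% |
| 20% / 40% | 1 | 0.483·0.20·1 = 9.7 | 47% | 26.9% |

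The rows with m = 1 are extreme bounds, since 30-day readmissions and reoperations are collected. The table does not give the bias in the CCI itself, which is a 0–100 score in which minor events carry less weight.

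**The case against.** **The strongest reply is that 30-day capture is plainly intended in both arms.** Table 2 marks it. SSI, reoperation and readmission are all defined to 30 days. Sample size allows for drop-out over that period, and Data monitoring plans a safety analysis at 30-day follow-up. Data collection methods describes visit windows and at least three contact attempts before a patient is declared lost. This stands. A reader might infer that laparoscopic patients are observed for less time and will therefore appear to have fewer complications; the schedule does not support that.

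**Nor are the CRFs confined to the inpatient stay.** One might infer this by joining the Data management sentence to the Table 2 column heading. But Post-intervention data includes the 90-day questionnaire and follow-up to 5 years, and the study exit form is part of the CRFs. This also stands.

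**The follow-up text excludes extra required visits, not routine follow-up or record review.** True, but it does not say that either is used to complete the day-30 entry.

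**An article may leave the mode of assessment to the full protocol.** Silence alone would be no finding. Here, though, the text states positively that the 90-day questionnaire is the only departure from usual follow-up. A trial-specific day-30 call would contradict that statement unless usual care already includes one.

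**The size is assumed throughout, and on a scale that is not the CCI.** This stands and limits the severity.

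**Conclusion.** The point holds as a moderate weakness. The plan schedules a 30-day complication assessment but, as written, leaves events after discharge to reach the primary outcome through routine care alone. Because a shorter laparoscopic stay is expected and complication assessment is not stated to be blinded, grade I–II events treated outside hospital may be under-recorded in that arm, which would favour the trial's hypothesis.

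The direction rests on two conditions: that stay is in fact shorter after laparoscopy, and that capture after discharge is incomplete. If routine care in these hospitals already obtains complete day-30 information in both arms, the bias is nil. Otherwise it ranges from negligible to material under the assumed figures. The documents do not show that a bias will occur, and they do not allow its size in CCI points to be estimated.

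**What to change.** Reconcile the follow-up text under Exclusion criteria and the CRF sentence in Data management with Table 2 by stating one day-30 ascertainment method, identical in both arms:

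- a short telephone contact by existing study staff, using a fixed list of complication questions;
- review of available hospital and primary-care records to day 30, completed before the CCI is closed;
- for patients already past day 30, the record review alone.

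Add a sensitivity analysis of the CCI restricted to Clavien-Dindo grade III or higher, whose detection should depend little on the date of discharge.

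The cost is one brief call per remaining patient, a minor amendment to the wording on departures from usual follow-up, and one extra analysis. Trial status reports 75 enrolled against a target of 192, so at that count 192 − 75 = 117 patients could still be covered by the call. Recorded morbidity may rise slightly in both arms. Acting early matters, because minor events not recorded near the time may be impossible to recover at analysis.

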### Surgical technique

The operations will be conducted according to the requirements of the patient’s underlying medical condition, for example whether the reason for surgery is perforation or obstruction.

For an obstruction in the right-sided colon or transversum, the aim will be primary resection and anastomosis. The anastomosis will be done extracorporeally to avoid fecal contamination. In the case of perforation with wide contamination in the critically ill patient, an ostomy alone will be considered instead of anastomosis or with a defunctioning stoma. For an obstruction in the left-sided colon, the aim will also be to perform a primary resection with anastomosis. Because of the elevated risk of anastomotic leakage, a defunctioning loop transversostomy or ileostomy will be considered even in the absence of perforation. Depending on the clinical condition of the patient, primary resection with end colostomy is also an option.

In the case of perforation and peritonitis, intra-abdominal lavage will be performed. If the reason for surgery is colorectal cancer, the operation will be performed according to CME principles.

In laparoscopic operations, decompression of the enlarged intestine will be carried out at the beginning of the procedure by making a small incision in the site planned for specimen removal. The wound will be protected by a wound protector. After making a purse-string suture, a small enterotomy will be performed in the intestinal wall, through which a suction tube will be inserted to decompress the bowel. After sufficient decompression, the enterotomy will be closed and the lid placed on the wound protector. After this, pneumoperitoneum will be created and the procedure carried out laparoscopically according to same principles as in elective surgery. In open surgery, either a midline or a horizontal incision will be made and the procedure carried out according to normal praxis. A separate decompression is not usually needed. The wound will be closed according to Israelsson’s technique with slowly absorbable monofilament sutures.

If needed, at any point of the protocol, for patient safety or any another reason, the allocated intervention will be modified or discontinued.

### Outcomes

The main endpoint of the study will be 30-day postoperative morbidity, which will be evaluated from the Comprehensive Complication Index (CCI) of all patients. CCI is the sum of all complications weighted on with their severity based on the Clavien-Dindo classification (CCI = √(*wC* + *wC*2 + … + *wCx*)/2) and has values ranging from 0 to 100 [24].

The secondary endpoints of the study are as follows.

#### Ninety-day mortality

Ninety-day mortality is death for any reason within 90 days of surgery (yes/no).

#### Surgical site infection (SSI)

SSI is defined as infections occurring up to 30 days after surgery (or up to 1 year after surgery in patients receiving implants) and affecting either the incision or the deep tissue at the operation site. SSI is divided into superficial incisional, deep incisional, and organ/space surgical site infections [25].

#### Intensive care unit (ICU)-free days

ICU-free days are defined as the number of days during which the patient is alive up to 30 days postoperatively minus days spent in the ICU (range 0–30).

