### Sample size

Sample size calculations will be based on previous studies, which report 48.3% 30-day postoperative morbidity after open surgery and 27.8% after laparoscopy [22]. The aim of the study is to show that postoperative morbidity is lower after laparoscopic surgery. Assuming *α* = 0.05 and a (?) power = 80, 87 patients are needed for both groups. The effect size is 0.54. Assuming a 10% patient drop-out rate during the 30-day follow-up period, a total of 192 patients, i.e., 96 in each group, is needed.

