### Statistical methods

The findings will be analyzed using SPSS (version 27 or higher) (IBM Corp., Armonk, NY, USA) for Windows. Both intention-to-treat and per-protocol analyses will be performed.

Between-group comparisons of continuous variables will be performed using Student’s *t* test or with the Mann–Whitney *U* test if heterogeneous variances persist. Categorical data will be compared using the *χ*^2^ test or Fisher’s exact test. Long-term survival will be analyzed using Cox regression or Kaplan–Meier’s analysis. Two-tailed *p* values will be reported. *P*-values ≤ 0.05 are considered significant. If data for a certain variable is missing the case will be removed from the analysis in question.

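### ICU-free days does not rank death worst, so some late deaths outscore survivors who needed intensive care, and the arm with more deaths can (not must) score better

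*Protocol article*

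**What the plan says.** The Outcomes section of the protocol article lists ICU-free days among the secondary endpoints and defines it as "the number of days during which the patient is alive up to 30 days postoperatively minus days spent in the ICU", with a stated range of 0 to 30. The definition contains no other rule for patients who die.

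The Statistical methods section gives only a general rule: "Between-group comparisons of continuous variables will be performed using Student’s" *t* test, or the Mann–Whitney *U* test if variances remain heterogeneous. It says nothing about deaths for this endpoint. All-cause death within 90 days is a separate yes/no secondary endpoint. The Objectives section expects mortality to differ between the arms, listing among the hoped-for benefits of laparoscopy "fewer wound complications, and lower risk of mortality".

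**The concern.** A higher count of ICU-free days will be read as a better outcome. That reading is safe only if no death can score above a survival. Under the stated definition death stops the count but keeps every day lived outside the ICU, so a late death on the ward retains a high score, while a survivor loses one point for each ICU day.

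The trial's own hypothesis is that mortality differs between arms, so the endpoint will be compared in the setting where this matters. If one arm has more late deaths with little ICU use and the other has more survivors with long ICU stays, the first can show the higher mean or the better ranks. This is not a detail left to an analysis plan: the scoring rule is fixed in the protocol.

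**Working it through.** **Inputs.** The definition and range come from the ICU-free days section. The arm size is from the Sample size section: "87 patients are needed for both groups", meaning 87 in each, since the same section then gives 96 in each group after drop-out. The article gives no ICU use, mortality or timing of death, so every arm-level figure below is an assumption. A death on day D is counted as D days alive.

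**1. Stated range.** Score = min(day of death, 30) − ICU days, with 30 in place of the day of death for survivors. Over all possible days of death and ICU stays the minimum is 0 and the maximum 30, as stated.

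**2. Order of individual patients.** A ward death on day D without ICU care scores D; a survivor with I ICU days scores 30 − I. The death scores higher when D > 30 − I, that is, when I > 30 − D.

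- Death on day 28: 28. Survivor with 5 ICU days: 30 − 5 = 25. The death ranks higher.
- Death on day 20 after 1 ICU day: 20 − 1 = 19. Survivor with 12 ICU days: 30 − 12 = 18. The death ranks higher.
- Death on day 25: 25. Survivor with 2 ICU days: 30 − 2 = 28. The survivor ranks higher.

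**3. Arm means, 8% affected (assumed).** The arms are alike except that 8% of patients survive with ICU care in one and die in the other. The difference (arm with deaths minus the other arm) is 0.08 × (mean score of those who die − mean score of those who survive). The second to fourth rows each change one assumption of the first.

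| Profile of the affected 8% | Die | Survive | Difference, days |
|---|---|---|---|
| Deaths on days 12–28 (mean 20) with 0–2 ICU days (mean 1); survivors with 8–18 ICU days (mean 13) | 20 − 1 = 19 | 30 − 13 = 17 | 0.08 × 2 = +0.16 |
| Deaths on days 2–28 (mean 15) | 15 − 1 = 14 | 17 | 0.08 × (−3) = −0.24 |
| 0–8 ICU days before death (mean 4) | 20 − 4 = 16 | 17 | 0.08 × (−1) = −0.08 |
| Survivors with 4–14 ICU days (mean 9) | 19 | 30 − 9 = 21 | 0.08 × (−2) = −0.16 |

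Changing the affected share only rescales a row: the first gives +0.08 at 4% and +0.24 at 12%. The sign depends on the timing of death and the ICU stays. With death scored 0, the first row becomes 0.08 × (0 − 17) = −1.36 days.

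**4. Whole arms of 87 (assumed counts).** Arm A has 9 ward deaths on day 25, 12 survivors with 7 ICU days (score 23) and 66 survivors without ICU care (score 30). Arm B has 4, 22 and 61.

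- As defined, A: (9 × 25 + 12 × 23 + 66 × 30)/87 = 2481/87 = 28.52. B: (4 × 25 + 22 × 23 + 61 × 30)/87 = 2436/87 = 28.00. The arm with more deaths scores higher (*t* test p = 0.24).
- Death scored 0, A: 2256/87 = 25.93. B: 2336/87 = 26.85. The order of the means reverses.

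**5. An extreme case, and what the remedy does not cure.** Arm A has 12 ward deaths on day 25 and no ICU use; arm B has 4 such deaths and 20 survivors with 7 ICU days.

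- As defined: 29.31 v 28.16, *t* test p = 0.002, Mann–Whitney p = 0.006, in favour of the arm with three times the deaths.
- Death scored 0: means 25.86 v 27.01. The Mann–Whitney probability that an arm A patient scores higher, with ties counted half, is still 0.553 (p = 0.09). Only 12 of 87 patients in A fall below the top score, against 24 of 87 in B, and a rank test responds to that.

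**The case against.** The definition is explicit, reproducible and consistent with its range. It does penalise death: a death on day D forfeits 30 − D days, and a death on day 3 scores at most 3. Ninety-day mortality is reported separately, so excess deaths would be visible. This is one of many secondary endpoints and leaves the primary endpoint untouched. Modest changes to the assumed profile give the opposite sign, and even the +0.16 days is only about 0.3 of its standard error (about 0.57 days at 87 per arm in that scenario). The significant example needs an extreme split.

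All of this stands as a limit on size. It does not remove the ordering fault in step 2, which needs no assumed rates, and a separate mortality endpoint does not change how ICU-free days is scored.

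A reader might infer more than the documents support:

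- *That death carries no penalty, or that the arm with more deaths will always look better.* Neither is true; three of the four scenarios in step 3 go the other way.
- *That ICU days during a readmission are lost*, because Table 2 marks "Need for postoperative intensive care/intensive care unit treatment" only under the hospital stay. The Post-intervention data section lists ICU days without limiting them to the index stay, 30-day readmission is itself an endpoint, and Table 2 has no row for several other collected outcomes. A missing mark does not show missing data.
- *That the Background's "a three times higher risk of failure to rescue, compared to elective surgery" makes a reversal likely.* That compares emergency with elective surgery, not laparoscopic with open, and says nothing about a difference between arms.

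**Conclusion.** The point holds in a limited form. As defined, ICU-free days can rank a death above a survival, whenever the survivor's ICU days exceed the days lost to death plus any ICU days of the patient who died. That follows from the definition alone.

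Whether it would mislead between arms cannot be settled from the article. Under the assumed 8% scenarios the difference for the arm with more deaths runs from −0.24 to +0.16 days, so a reversal is possible, not certain. The counts in the arms of 87 likewise show possibility, not likelihood. This is a cheap improvement to a secondary endpoint; it does not threaten the trial's main conclusion.

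**What to change.** In the ICU-free days definition, state that any patient who dies by day 30 ranks below every survivor, and that alive days minus ICU days are computed only for patients alive at day 30. Name the Mann–Whitney test for this endpoint, since the ranking needs it. Scoring deaths 0 is the simpler alternative and also works for means, but a survivor with 30 ICU days would then tie with a death.

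Report the number of deaths by day 30 in each arm directly beside the result, because a rank test can still lean towards the arm with less ICU use (step 5).

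The cost is a sentence or two. No new data are needed: the present definition already requires days alive to day 30 and ICU days. The downside is that early and late deaths get the same score. The change should be recorded as an amendment before this endpoint is compared between arms.
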